### Justification of sample size

With n ≈ 100,000 in each BMI time point before and after the school reform, we have 80% power (alpha level = 0.05) to detect a difference of 0.04 BMI points assuming a standard deviation of 3.2 BMI points (data from EYHS). With n ≈ 2,000 in each PA time point before and after the reform, we have 80% power (alpha level = 0.05) to detect a difference in moderate-vigorous PA of approximately 2 min/day assuming a standard deviation of 24 min/day (data from SPACE).

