#### Body mass index

BMI calculated as weight divided by height-squared is collected via the nationwide surveillance database *The Child Database*. In Denmark, all school-aged children are offered a preventive health examination obtained by either school nurses or medical doctors according to law. In 2011, it became compulsory for all Danish municipalities to annually report data on height and weight to *The Child Database* via the Danish Board of Health Electronic Report System. Data are considered complete from 2012 and onwards, and from this time data on approximately 100,000 children aged 6–7 years (pre-preparatory classes), 9–13 years (intermediate classes) and 14–15 years (lower secondary education) are available annually. In the pre-preparatory classes the first assessment obtained is reported to *The Child Database*. If several measurements are conducted during the intermediate classes the measurements obtained closest to the child’s 11th birthday will be reported. In the lower secondary education classes the last measurement obtained before the child finishes school will be reported. Data from 2012 to 2018 will be extracted from *The Child Database* in 2019 (Fig. 4).

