### Statistical methods

Descriptives of the cohort will be obtained for characterization and representativeness. Interrupted time-series (ITS) analysis will be used as the overall statistical method. Based on at least two repeated cross-sectional assessments before and after the introduction of the school reform, ITS estimates the pre-reform slope, the change in level around the time of introduction of the reform accounting for the pre-reform trend, and the change in slope after the reform. The results of the change in level and the change in slope represent the estimates of the effect of the reform assuming a linear before- and after time trend. With regard to BMI, *The Child Database* provides sufficient pre- and post-reform data points to investigate trends. With respect to PA, pre-and post reform analysis will be conducted.

Multi-level regression and significance tests will be utilized for analyses in both parts of the study (the effect and process evaluation), as qualitative analyses will be used for analyses with respect to the process evaluation.

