## Discussion

The public school reform implemented in the Autumn of 2014 by the Danish government provides a unique opportunity for evaluating the effectiveness of this ambitious nation-wide policy-driven school-based PA promotion initiative. By international comparison, the magnitude of the strengthened focus on PA as a key component of public school life is exceptional. Access to historical data on objectively measured PA and body composition provides a rare opportunity to evaluate the effect of this ambitious legislation on PA- and BMI levels in school-aged children and adolescents. Further, in combination with the process evaluation the study aims to understand the different implementation processes and thereby the expected variation in uptake of the reform on PA. As mentioned earlier, several randomized controlled studies have evaluated the effect of various school-based PA promotion interventions [11]. Because many randomized controlled studies evaluating the effectiveness of school-based PA have been researcher-led interventions and typically conducted in non-representative samples they often have poor external validity. When possible, complementing any evidence on effectiveness from randomized controlled studies with that from observations based on natural experiments are therefore highly valuable. Thus, the present project will significantly advance and complement the evidence on the effectiveness of school-based PA interventions. The school-level data characterizing how individual schools have implemented the PA requirement prompted by the reform will be an important resource to support and help explain findings in the effectiveness analysis, including variations in effect. Furthermore, these observations can be used to establish a number of ‘best practice’ examples, which are important for the government, municipalities, schools and other non-governmental organizations working with promotion of PA in schools.

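### The 80% power for 0.04 BMI points is a two-point figure with no year-to-year variation; it is not the detectable change for the planned interrupted time-series estimates

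*Protocol article*

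**What the plan says.** The section Justification of sample size gives the only statement of BMI precision: "With n ≈ 100,000 in each BMI time point before and after the school reform, we have 80% power (alpha level = 0.05"). The target difference there is 0.04 BMI points, and the SD of 3.2 is taken from one of the historical studies.

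The section Statistical methods defines the effect differently: "The results of the change in level and the change in slope represent the estimates of the effect of the reform assuming a linear before-". Linearity is thus assumed on both sides of the reform. The section regards the BMI register as having enough time points before and after it. On the model it says only: "Multi-level regression and significance tests will be utilized for analyses in both parts of the study". The levels are not named, and neither a year-level error term nor autocorrelation is mentioned.

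The section Body mass index sets the window: "Data from 2012 to 2018 will be extracted from" the national register, which municipalities report to annually. The Discussion dates the reform to autumn 2014. The design sections say that there is no control group.

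**The concern.** Exposure to the reform varies only with calendar time, because every public school entered it together. Information about a break in the national series therefore comes from the number of time points and from how far annual means scatter around a line. The number of children measured each year adds little to that. Anything shared by all children in a year (who is examined, when they are measured, which measurement is reported) is not averaged out by measuring 100,000 of them.

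The stated power leaves this out. It also sizes a contrast of one time point before with one after, which Study design and objectives itself rejects because it ignores the earlier trend. Two things are at stake. Readers may believe that a 0.04 shift can be detected with 80% power when the planned estimate cannot do so. And if the same child-level error were carried into the test, its intervals would be too narrow.

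**Working it through.** **Inputs from the article.** n = 100,000 per time point, SD 3.2, alpha 0.05, power 80%, stated difference 0.04 (Justification of sample size); window 2012 to 2018 (Body mass index); reform in autumn 2014 (Discussion).

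**Assumptions.** Two-sided test; one mean per year, so 7 points; jump evaluated at the first post-reform year; between-year SD tau, which the article does not give and which is shown as a range.

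**1. Reproduce 0.04.** SE of one annual mean = 3.2/√100,000 = 0.01012. Detectable difference between two means = (1.960 + 0.842) × 0.01012 × √2 = 0.0401. Power for 0.04 is 79.8%. A one-sided test would give 87.5% and does not fit. The figure therefore contains child-level error only.

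**2. ITS coefficients, tau = 0.** With four parameters (intercept, slope, level change, slope change), the variance of the level change, in units of the squared SE of one annual mean, is the sum over the two segments of 1/m + d²/Sxx. Here m is the number of years in the segment, d the distance from its mean year to the evaluation year, and Sxx its sum of squares in time. The variance of the slope change is the sum of 1/Sxx.

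- 2014 coded pre (2012–14 / 2015–18): level (1/3 + 2²/2) + (1/4 + 1.5²/5) = 3.033, root 1.742; slope 1/2 + 1/5 = 0.7, root 0.837.
- 2014 coded post (2012–13 / 2014–18): level (1/2 + 1.5²/0.5) + (1/5 + 2²/10) = 5.6, root 2.366; slope 1/0.5 + 1/10 = 2.1, root 1.449.

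| | 2014 pre | 2014 post |
|---|---|---|
| SE of level change | 0.0176 | 0.0239 |
| Detectable level change (2.802 × SE) | 0.049 | 0.067 |
| Power for 0.04, Φ(0.04/SE − 1.96) | 62% | 39% |
| Detectable slope change per year | 0.024 | 0.041 |

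The evaluation point matters. With 2014 coded pre and the jump placed halfway between 2014 and 2015, the level variance is (1/3 + 1.5²/2) + (1/4 + 2²/5) = 2.508, root 1.584. The detectable change is then 2.802 × 1.584 × 0.01012 = 0.045, and power for 0.04 is Φ(0.04/0.01603 − 1.96), about 70%.

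**3. If year-level error is left out of the test.** Independent year deviations multiply the true SE of every coefficient by k = √(1 + (tau/0.01012)²), so the type I error is 2 × (1 − Φ(1.96/k)).

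| tau | k | Type I error per coefficient |
|---|---|---|
| 0 | 1.00 | 5.0% |
| 0.005 | 1.12 | 7.9% |
| 0.01 | 1.41 | 16% |
| 0.02 | 2.22 | 38% |
| 0.03 | 3.13 | 53% |

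It doubles to 10% at tau of about 0.0066. Levels for child, school or municipality would not change this, because a year shock is common to all of them.

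**4. If year-level error is included.** Fit the segmented regression to the 7 annual means with their own residual variance: 7 − 4 = 3 df, t critical value 3.18. Simulation with independent years returns a type I error of 5%. 80% power needs a true change of about 4.3 SE, where SE = 1.742 × √(0.01012² + tau²) with 2014 coded pre.

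| tau | Detectable level change | Power for 0.04 |
|---|---|---|
| 0 | 0.08 | 35% |
| 0.01 | 0.11 | 21% |
| 0.02 | 0.17 | 12% |
| 0.03 | 0.24 | 8% |

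**The case against.** The strongest reply is that a sample-size sentence is not a test specification. A reader might infer that the BMI effect will be judged against child-level error alone, and that ordinary year-to-year noise will therefore be declared a reform effect far more often than 5% of the time. The article does not support that. Statistical methods plans multi-level regression without naming its levels, so a year-level term is neither stated nor excluded. No between-year SD is given, and at 0.005 the rate would be only 7.9%. The rates in step 3 are therefore conditional on two things the article leaves open.

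It can also be said that random-effect levels, autocorrelation and degrees of freedom normally belong in an analysis plan, which is not shown. That is fair, and silence on them is not an error in a condensed article. Seven annual points is also an inference from the window and annual reporting, since the figure showing the BMI time points is not available.

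These replies do not reach the 0.04 itself. The article chose to state a power and a detectable difference, and they do not belong to the estimates it names as the effect. That holds even with no year-to-year variation, as step 2 shows.

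**Conclusion.** The stated power does not describe the planned BMI analysis. The figure of 0.04 is correct for two annual means with zero year-to-year variation. For the ITS level change on 7 annual means, still with zero year variation, the detectable change is about 0.049 or 0.067 depending on how 2014 is coded, and power for 0.04 is about 62% or 39%. These values depend on annual points and on evaluating the jump at the first post-reform year.

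Type I error is a conditional risk, not a demonstrated fault. It arises only if the test omits year-level error, and its size depends on a between-year SD that the article does not give. Because the SE of an annual mean is only about 0.010, small departures from a straight line would be enough to matter.

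**What to change.** In Justification of sample size, say that 0.04 refers to two time points with no year-to-year variation. Add the detectable ITS level change and slope change for an assumed range of between-year SD, for example 0 to 0.03, and state how 2014 is coded and where the jump is evaluated.

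In Statistical methods, state that the BMI level and slope changes are tested with between-time-point variance in the error term and small-sample degrees of freedom. This can be done by regression on time-point means or by a random effect for time point. If measurement dates allow, use finer time points with season terms and autocorrelated errors, so that the between-time variance is estimated with more degrees of freedom.

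No new data are needed. The cost is wider intervals and a less favourable detectable change, as step 4 shows for 3 df. The 3-df test is also not a complete safeguard: in simulation with a between-year autocorrelation of 0.5 and between-year SD up to 0.05, its type I error was 5% to 7% for the level change and 5% to 11% for the slope change.

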#### Pre-reform study populations

As previously stated, there are no routine surveillance systems of PA in Danish school children; therefore, we identified individual studies with information on these variables. The validity of self-report as a sole source of information is limited in this age group and may potentially also drift over time, which would defeat the purpose of our investigation [20]. Thus, objectively measured PA data collected in four school-based studies before 2014 comprise the historical data used to evaluate pre-reform PA levels and trends. The four studies are 1) The European Youth Heart Study (EYHS) conducted in 1997–98, 2003–04 and 2009–10, 2) When Cities Move Children (WCMC) conducted in 2010 and 2012, 3) Childhood Health, Activity, and Motor Performance School Study Denmark (CHAMPS-DK) conducted in 2009, 2010 and 2012, and 4) School site, Play Spot, Active transport, Club fitness and Environment (SPACE) conducted in 2010 and 2012. Accelerometry was used to assess PA in all four studies. Sampling and recruitment of children and adolescents included in these four studies have been described elsewhere [21–24]. These studies comprise PA data on approximately *n* = 2,500 1st to 9th grade children from 44 schools in 7 municipalities in the Region of Southern Denmark and the Capital Region of Denmark. An overview of the historical studies and study populations is presented in Fig. 2.

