#### Post-reform study population

To enable evaluation of post-reform PA levels it is imperative to conduct an additional data collection after the introduction of the school reform in 2014. Thus, a new cross-sectional data collection was initiated in 2017 including school-aged children and adolescents that broadly represent the source population of the four historical studies (Fig. 2). Consequently, the same schools and age-groups as in the four historical studies were invited to participate in the PHASAR study. Two of the historical studies (CHAMPS-DK and SPACE) introduced PA promoting initiatives as part of their study; to minimize any influence from participation in these interventions we chose only to include and recruit control schools from these studies (Fig. 2). The schools were contacted continually in 2017 and invited to participate in the study. A total of 36 schools were invited in 2017 and 31 schools accepted the invitation to participate.

All parents or guardians of the invited children received an invitation that explained the objective, content and procedures of the study. Children received similar oral information at the schools provided by the research team. If parents or guardians, or the child, did not want to participate, they were able to withdraw at any stage. A child or an adolescent was found eligible to participate if 1) the child attended one of the public schools and age groups (grades) that had already been included in one of the four pre-reform studies, and 2) the child did not suffer from any physical disabilities or injuries preventing physical activity.

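### The physical activity power figure (about 2 min/day at 80% power) makes no allowance for school clustering, and its pre-reform sample size fits only a pooled pre-post contrast

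*Protocol article*

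**What the plan says.** All places are in the protocol article.

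- **Justification of sample size:** the physical activity (PA) claim is 80% power at alpha 0.05 "to detect a difference in moderate-vigorous PA of approximately 2 min/day assuming a standard deviation of 24 min/day", with n of about "2,000 in each PA time point before and after the reform" and the SD taken from one of the historical studies (SPACE). No ICC, cluster size or design effect is mentioned.
- **Post-reform study population:** "A total of 36 schools were invited in 2017 and 31 schools accepted the invitation to participate". The Abstract puts the post-reform sample at over 2,000 children. The schools were those of the historical studies.
- **Pre-reform study populations:** about 2,500 "1st to 9th grade children from 44 schools in 7 municipalities", over four studies with 3, 2, 3 and 2 waves between 1997-98 and 2012.
- **Statistical methods:** "Multi-level regression and significance tests will be utilized for analyses in both parts of the study". For PA this section announces a pre- and post-reform analysis and reserves the statement about sufficient data points for trends to BMI.
- **Abstract (Methods)** and **Strengths and limitations, Study design:** interrupted time-series (ITS) analysis is announced for both PA and BMI, for levels and trends.
- **Study design and objectives:** a simple comparison of one assessment before with one after is criticised because it ignores earlier trends.

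**The concern.** Children in one school share timetable, playground, staff and the school's own way of implementing the reform, so their activity levels are correlated. The planned multi-level model recognises this; the power statement does not. If the statement uses a formula for independent children, the design does not have 80% power for about 2 min/day unless school effects are almost unchanged between periods.

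The input of about 2,000 per time point also needs a meaning. A pre-reform total of about 2,500 cannot provide 2,000 at each of several pre-reform time points. It can provide 2,000 only as one pooled sample.

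At stake is how the PA result is read. This is the only stated justification of the PA sample size, and a reader who takes 2 min/day at face value will overrate how informative a null or small estimate is.

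**Working it through.** **Inputs from the article:** SD 24 min/day; n about 2,000 before and after; alpha 0.05 (sidedness not stated, two-sided taken); power 80%; 31 schools after the reform; about 2,500 pre-reform children from 44 schools in 3 + 2 + 3 + 2 = 10 study-waves.

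**Inputs assumed, because the article does not give them:** ICC 0.01, 0.02, 0.05 or 0.10; between-period correlation of school effects r = 0, 0.5 or 0.8.

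**Step 1. Reproduce the stated figure.** Detectable difference = (1.960 + 0.842) × SD × √(2/n) = 2.802 × 24 × √(2/2000) = **2.13 min/day**, which rounds to the stated figure. One-sided, it would be 1.89. At exactly 2 min/day the two-sided power is 75%. The BMI figure follows from the same formula: 2.802 × 3.2 × √(2/100,000) = 0.040. There is no room in the PA figure for a design effect.

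**Step 2. Add clustering to the pre-post contrast.** Cluster size m = 2000/31 = 64.5. For the same schools in both periods,

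DE = (1 − ICC) + m × ICC × (1 − r), and detectable difference = 2.126 × √DE.

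With r = 0 this is the usual 1 + (m − 1) × ICC. For simplicity, 31 schools and 2,000 children are used in both periods.

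| ICC | DE, r = 0 | min/day | DE, r = 0.5 | min/day | DE, r = 0.8 | min/day |
|---|---|---|---|---|---|---|
| 0.01 | 1.64 | 2.72 | 1.31 | 2.44 | 1.12 | 2.25 |
| 0.02 | 2.27 | 3.20 | 1.63 | 2.71 | 1.24 | 2.37 |
| 0.05 | 4.18 | 4.34 | 2.56 | 3.40 | 1.60 | 2.69 |
| 0.10 | 7.35 | 5.77 | 4.13 | 4.32 | 2.19 | 3.15 |

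At ICC 0.05, power for 2.13 min/day is 28%, 42% and 60% for r = 0, 0.5 and 0.8.

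The penalty is gone (DE ≤ 1) only if m × (1 − r) ≤ 1, that is r ≥ 1 − 1/64.5 = 0.98.

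**Step 3. Check the pre-reform sample size.**

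- All waves pooled: 2.802 × 24 × √(1/2500 + 1/2000) = 2.02 min/day. On this reading the stated n does no numerical harm.
- Trend-adjusted: fit a line through the pre-reform waves, project it to 2018 and compare with 2,000 children. Assume 10 equal waves of 2,500/10 = 250. With EYHS waves coded 1998, 2004 and 2010, the mean year is 2008.7 and the sum of squared deviations is 176.1. The variance factor is 1/2500 + (2018 − 2008.7)²/(250 × 176.1) + 1/2000 = 0.000400 + 0.001965 + 0.000500 = 0.002865. The detectable difference is 2.802 × 24 × √0.002865 = **3.6 min/day** before any clustering (3.5 if those waves are coded mid-season).

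Clustering makes the trend-adjusted figure larger. The design effects in Step 2 cannot simply be multiplied in, because they use the post-reform cluster size. Before the reform there are only about 2500/44 = 57 children per school over all waves together, hence fewer per school and wave.

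**The case against.** **The sum itself is right.** It is. The fault lies in the independence assumption, and nobody should infer a calculation error.

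**The same schools were measured before and after.** This is the best defence. Stable school differences cancel in a pre-post contrast, so r = 0 is the least fitting row of assumptions. But full recovery needs r of about 0.98. The waves lie roughly 5 to 20 years before 2017/18, the 44 historical schools were not all re-measured (36 invited, 31 enrolled), and the Discussion expects uptake of the reform to vary. Part of the penalty is therefore likely to remain. How much cannot be said from the document.

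**The planned model handles clustering.** It does so for the standard errors of the results, but it does not make the advance power statement correct.

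**The pre-reform n can be read as one pooled sample.** This is fair. The Statistical methods section supports it for PA, and pooling gives 2.02 min/day. If schools were of equal size, 2,500 × 36/44 is about 2,045, close to the stated 2,000. A reader might infer that the sample-size section flatly contradicts the historical total, or that each wave held 250 children. The article supports neither: the wording allows pooling, and the wave sizes belong to a figure that is not shown here. What stands is narrower. The pooled reading means a contrast without trend adjustment, which does not match the ITS promised for PA elsewhere.

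**Conclusion.** The point holds, with two parts of unequal weight.

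**Main part.** The claim of 80% power for about 2 min/day rests on independent children and omits the clustering that the design has and the analysis plan recognises. For the pre-post contrast, the detectable difference is about 2.25 to 5.8 min/day over ICC 0.01 to 0.10 and r from 0 to 0.8. The true place in that range is unknown, since neither quantity is in the article. A low ICC with stable school effects would leave the figure close to 2.

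**Secondary part.** The stated pre-reform n is tenable only with all waves pooled. If the PA effect is instead estimated against a pre-reform trend, the figure is about 3.6 min/day before clustering, assuming ten equal waves, and larger after it.

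A reader might go further and conclude that the study cannot detect a relevant effect, that its PA results will be invalid, or that a null result is bound to be misread. The document does not support this: it names no minimum relevant difference, plans a multi-level analysis, and nowhere says how a null result will be interpreted. The fault is in the justification as stated.

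**What to change.** Restate the PA part of the sample-size section:

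1. Estimate the ICC for moderate-to-vigorous activity and the between-period correlation of school effects from the historical studies, several of which measured more than one wave. Report both, with a range if they are imprecise.
2. Apply a design effect using the actual numbers of children and schools before and after the reform, rather than 2,000 at each time point.
3. Say which contrast the figure describes. For the pooled pre-post contrast, the assumed ranges above give roughly 2.25 to 5.8 min/day, to be replaced by the estimate from step 1. For a trend-adjusted contrast, compute it from the actual wave dates and sizes with clustering included; the pooled range must not be used for it.
4. Bring the Abstract, Statistical methods and Strengths and limitations sections into line on whether PA is analysed by ITS or by a pre-post comparison.

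The cost is a short recalculation on data already held, plus text. No extra recruitment is needed. The downside is a less favourable stated figure.
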